## Abstract

**Background:**

Elevated cardiac troponin, which indicates cardiomyocyte injury, is common after acute ischemic stroke and is associated with poor functional outcome. Myocardial injury is part of a broad spectrum of cardiac complications that may occur after acute ischemic stroke. Previous studies have shown that in most patients, the underlying mechanism of stroke-associated myocardial injury may not be a concomitant acute coronary syndrome. Evidence from animal research and clinical and neuroimaging studies suggest that functional and structural alterations in the central autonomic network leading to stress-mediated neurocardiogenic injury may be a key underlying mechanism (ie, stroke-heart syndrome). However, the exact pathophysiological cascade remains unclear, and the diagnostic and therapeutic implications are unknown.

**Objective:**

The aim of this CORONA-IS (Cardiomyocyte injury following Acute Ischemic Stroke) study is to quantify autonomic dysfunction and to decipher downstream cardiac mechanisms leading to myocardial injury after acute ischemic stroke.

**Methods:**

In this prospective, observational, single-center cohort study, 300 patients with acute ischemic stroke, confirmed via cerebral magnetic resonance imaging (MRI) and presenting within 48 hours of symptom onset, will be recruited during in-hospital stay. On the basis of high-sensitivity cardiac troponin levels and corresponding to the fourth universal definition of myocardial infarction, 3 groups are defined (ie, no myocardial injury [no cardiac troponin elevation], chronic myocardial injury [stable elevation], and acute myocardial injury [dynamic rise/fall pattern]). Each group will include approximately 100 patients. Study patients will receive routine diagnostic care. In addition, they will receive 3 Tesla cardiovascular MRI and transthoracic echocardiography within 5 days of symptom onset to provide myocardial tissue characterization and assess cardiac function, 20-min high-resolution electrocardiogram for analysis of cardiac autonomic function, and extensive biobanking. A follow-up for cardiovascular events will be conducted 3 and 12 months after inclusion.

**Results:**

After a 4-month pilot phase, recruitment began in April 2019. We estimate a recruitment period of approximately 3 years to include 300 patients with a complete cardiovascular MRI protocol.

**Conclusions:**

Stroke-associated myocardial injury is a common and relevant complication. Our study has the potential to provide a better mechanistic understanding of heart and brain interactions in the setting of acute stroke. Thus, it is essential to develop algorithms for recognizing patients at risk and to refine diagnostic and therapeutic procedures.

**Trial Registration:**

Clinicaltrials.gov NCT03892226; https://www.clinicaltrials.gov/ct2/show/NCT03892226.

**International Registered Report Identifier (IRRID):**

DERR1-10.2196/24186

## Introduction

### Background

Elevated cardiac troponin (cTn), which is a sign of myocardial injury, frequently occurs in the early phase after an acute ischemic stroke (AIS) and is associated with poor functional outcome, especially increased mortality [1,2]. Using high-sensitivity assays, cTn is detectable in more than 90% of stroke patients; 30%-60% have at least one cTn above the assay-specific 99th percentile upper reference limit (URL) [2,3]. Approximately 5%-20% show a rise/fall pattern indicating acute myocardial injury according to the fourth universal definition of myocardial infarction (MI) [4]. In the latter group, acute coronary syndrome has to be suspected [4-6]. Following the American guidelines (American Heart Association/American Stroke Association), it is specifically recommended to measure cTn in stroke patients [7,8]. However, recommendations on how to deal with elevated cTn in the context of AIS remain vague [8]. Furthermore, expert consensus documents on practical considerations on the clinical use of cTn list ischemic stroke as one of the illnesses that leads to clinical uncertainty in the context of interpretation of elevated cTn [9].

The phenomenon of acute brain injuries (including an ischemic stroke and intracranial hemorrhage) leading to cardiac complications, including elevated cardiac enzymes, is known for a long time. In reference to AIS, it has recently been described as stroke-heart syndrome (SHS) [10-13]. However, the exact pathophysiologic background of myocardial injury (ie, cTn elevation) after stroke is not entirely understood [13,14]. Several hypotheses have been discussed. Besides concomitant acute MI caused by atherothrombotic coronary artery disease (type 1 MI), situations of oxygen supply/demand mismatch have to be considered as underlying reasons. For example, tachyarrhythmia, hypotension/shock, anemia, or respiratory failure, which are frequently seen in stroke patients, can lead to a demand ischemia [4,15]. Furthermore, systemic conditions such as sepsis or chronic kidney disease may cause or facilitate myocardial injury [16].

In the TRELAS (Troponin Elevation in Acute Ischemic Stroke) study, patients with AIS with markedly elevated cTn were significantly less likely to have a corresponding culprit lesion on coronary angiography when compared with age- and sex-matched patients with non-ST elevation acute coronary syndrome (ACS; showing no significant difference in the degree of cTn elevation) [17]. Together with the finding that half of the patients with AIS with markedly elevated cTn had no coronary artery disease at all, this implies that alternative mechanisms beyond ACS may play an important role [17]. This is supported by animal research and clinical and neuroimaging studies, suggesting that stroke-associated myocardial injury may originate from structural and/or functional interference within the central autonomic nervous system (CAN) with an overshooting sympathetic response [18-20]. On a cellular basis, it is assumed that excessive catecholamine and cortisol levels lead to an increased sarcoplasmic calcium influx with a consecutive hypercontraction of the sarcomeres, electrical instability, and metabolic and oxidative stress. Consequently, these pathological mechanisms can induce a contraction band necrosis and interstitial inflammatory reaction [12,21]. In summary, elevated troponin levels are frequent, and the underlying pathologies can be manifold, ranging from concomitant type 1 MI, demand ischemia, and chronic structural cardiac disease to systemic conditions. However, especially in situations with acute cTn elevation after AIS, the CAN seems to play an important role in the development of myocardial injury not only by triggering direct myocardial toxicity but also by facilitating situations of demand ischemia [13,14,22]. Nonetheless, the exact cascade of events remains mostly unclear, and when it comes to diagnostic procedures and treatment of affected patients, therapeutic options lack good scientific evidence [8].

### Objective

The aim of the Cardiomyocyte injury following Acute Ischemic Stroke (CORONA-IS) study is to gain mechanistic insights into stroke-associated myocardial injury. We intend to provide a detailed characterization of (1) myocardial tissue; (2) myocardial, ventricular, and atrial function; and (3) associated autonomic dysfunction by using multimodal diagnostic measures.

## Methods

### Study Design

The CORONA-IS study is an investigator-initiated, prospective, observational, single-center cohort study that aims to include 300 patients with AIS. In November 2018, the Ethics Committee of the Charité-Universitätsmedizin Berlin, Germany (EA4/123/18), approved the study. All study procedures are carried out in accordance with the principles of Good Clinical Practice and the Declaration of Helsinki. The study was pre-registered under clinicaltrials.gov, NCT03892226. All patients with AIS admitted to the hospital within 48 hours of symptom onset are listed in a hospital-based registry as part of an assessment of high-sensitivity cTn (hs-cTn) development in patients with AIS. All study patients have to fulfill the study inclusion criteria listed in Textbox 1, and all participants have to provide written informed consent (for exclusion criteria refer to Textbox 2).

Inclusion criteria.ability to provide informed consentage ≥18 yearsdiagnosis of acute ischemic stroke and hospital admission within 48 hours of symptom onsetvisible diffusion-weighted imaging lesion in cerebral magnetic resonance imagingrepeated measurement of high-sensitivity cardiac troponin within 24 hours of admission

Exclusion criteria.pregnancy or breastfeedingimpaired renal function (estimated glomerular filtration rate <30 ml/min/1.73 m^2^)contraindications to undergo magnetic resonance imaging (eg, cardiac pacemaker, implantable cardioverter-defibrillator, and cerebral clips)persistent or permanent atrial fibrillation (patients with paroxysmal atrial fibrillation will be included if they are in sinus rhythm at admission or during cardiac monitoring of the stroke unit)ST-elevation in electrocardiogram fulfilling criteria of myocardial ischemiahistory of cardiac intervention (eg, coronary artery bypass surgery or percutaneous coronary intervention) within the last 4 weeks

Depending on serial measurements of hs-cTn during the acute hospital stay (assay characteristics: hs troponin T, Roche Elecsys, Gen 5; 99th percentile upper reference limit=14 ng/l; 10% coefficients of variation (CV) precision=13 ng/l; limit of detection=5 ng/l) and according to the fourth universal definition of MI, 3 groups are defined (Table 1) [4]. We aim to include 100 patients in each group. The cTn values are based on at least two blood exams: the first one at hospital admission and a control measurement within 24 hours after admission.

**Table 1 table1:** Definition of the 3 groups based on patients’ high-sensitivity cardiac troponin values.

Group	Description	hs-cTn^a^ values (URL^b^=14 ng/l)
Group 1	Normal hs-cTn levels	Both hs-cTn levels ≤URL
Group 2	Chronic myocardial injury (elevated but stable cTn levels)	At least one hs-cTn level >URL but *no* rise/fall (>20%) in serial measurements
Group 3	Acute myocardial injury (dynamic elevation)	At least one hs-cTn level >URL *and* rise/fall (>20%) in serial measurements^c^

^a^hs-cTn: high-sensitivity cardiac troponin.

^b^URL: upper reference limit (=14 ng/l).

^c^Or initial cTn value ≤URL and second value >URL+increase >50% URL (ie, 7 ng/l).

In addition to routine clinical procedures (refer to the *Baseline Visit* section), study patients receive a baseline assessment, an additional blood draw for biobanking, 3 Tesla (3T) cardiovascular magnetic resonance imaging (CMR), transthoracic echocardiography (TTE), and a 20-min high-resolution electrocardiogram (ECG) for a comprehensive assessment of cardiac autonomic function as well as a questionnaire testing cognitive function and the perception of stress. Furthermore, 3 and 12 months after discharge, patients will be followed up via structured telephone interviews for cardiovascular events and clinical outcomes (Figure 1).

**Figure 1 figure1:**
[figure not shown]
Study procedure of the Cardiomyocyte injury following Acute Ischemic Stroke study. Patients with a confirmed diagnosis of acute ischemic stroke via magnetic resonance imaging within 48 hours of symptom onset are eligible for inclusion. Patients receive a baseline visit, transthoracic echocardiography, 20-min electrocardiogram recording, blood sampling for biobanking, and cognitive testing within the first 2 days after enrolment. 3T cardiovascular magnetic resonance imaging takes place 3-5 days after symptom onset. Telephonic follow-up for cardiovascular events and functional outcomes will be conducted after 3 and 12 months. CMR: cardiovascular magnetic resonance imaging; d: day; ECG: electrocardiogram; MoCA: Motreal-Cognitive-Assessment; PSS: Perceived Stress Scale; TTE: transthoracic echocardiography; y: year.

### Participants

Patients with a diagnosis of AIS, defined by a diffusion-weighted imaging lesion on magnetic resonance imaging (MRI), and hospital admission within 48 hours of symptom onset are included in the study. The study is carried out at the Department of Neurology, Charité-Universitätsmedizin Berlin, Campus Benjamin Franklin, Berlin, Germany.

### Baseline Visit

The baseline assessment of the study patients includes demographics, medical history, medication, and information about the current stroke (time of symptom onset, time of hospital admission, and treatment including thrombolysis or thrombectomy). Stroke severity is classified using the National Institutes of Health Scale Score. The degree of disability is assessed using the modified Rankin Scale score. The presence of chest pain and dyspnea at admission and before the event is documented. Cognitive function and the individual perception of stress will be assessed via 2 questionnaires: Perceived Stress Scale and Montreal-Cognitive-Assessment [23,24]. In addition, the results of routine diagnostic procedures and stroke unit monitoring (eg, vital signs, 12-lead ECG, laboratory results, cerebral computed tomography imaging/MRI, and ultrasound of the brain-supplying arteries) are recorded.

### Cardiovascular MRI Protocol

Patients receive a 3T cardiovascular MRI (CMR). The examination is performed on a 3T MR scanner (Siemens Magnetom Prisma fit 3T, Siemens) using ECG for cardiac gating.

The detailed CMR protocol is depicted in Figure 2. Initially, for localizing, a half-Fourier acquisition single-shot turbo spin-echo (HASTE) sequence is conducted. Second, to evaluate the morphology and function of the left ventricle (LV) and right ventricle (RV), *steady-state free-precession cine images* (SSFP) are acquired during repeated breath-holds. Data are obtained for 3 long axes (4-chamber [4Ch], 3-chamber [3Ch], and 2-chamber [2Ch] view) and RV (imaging parameters: repetition time [TR] 45.78 ms, echo time [TE] 1.43 ms, flip angle [FA] 80°, and slice thickness 6.0 mm) and short axes stack—after contrast media application—to cover the LV (imaging parameters: TR: 44.80 ms, TE: 1.4 ms, FA: 58°, and slice thickness 7.0 mm, no gap). Furthermore, after cine long axis, 3 cine short axes (base, middle, and apex) are conducted, serving as a base for mapping imaging (imaging parameters: TR: 44.80 ms, TE: 1.4 ms, FA: 58°, and slice thickness: 7.0 mm). Motion-corrected *T2 mapping* is conducted using a fast low-angle shot (FLASH) gradient echo sequence in a 4Ch view and 3 short axis views (SAX) as basal, medial, and apical slices. T2 maps are based on images with T2 preparation times of 0/30/55 ms, slice thickness of 6.0 mm, TR of 251.49 ms, and TE of 1.32 ms.

Postcontrast imaging is performed after intravenous injection of 0.15 mmol/kg body weight Gadobutrol (Gadovist, Bayer Healthcare). *Focal fibrosis imaging* (late gadolinium enhancement [LGE]) is conducted 10 min after Gadobutrol application. LGE imaging is performed using a phase-sensitive inversion recovery sequence (PSIR) in the same slice position as cine imaging (4Ch, 3Ch, and 2Ch view; imaging parameters: TR: 750.0 ms, TE: 1.55 ms, FA: 20°, and slice thickness: 7.0 mm) as well as full coverage of the LV in a short axis package (imaging parameters: TR: 1002.4 ms, TE: 1.24 ms, FA: 55°, and slice thickness: 8.0 mm). TI was adapted to suppress the myocard.

**Figure 2 figure2:**
[figure not shown]
3T cardiovascular magnetic resonance imaging protocol. Workflow of the cardiovascular magnetic resonance imaging sequences conducted. 2Ch: 2-chamber view; 3Ch: 3-chamber view; 4Ch: 4-chamber view; 3T: 3 Tesla; LGE: late gadolinium enhancement; mv: midventricular; SAX: short axis view; SSPF: steady-state free-precession.

Finally, for further myocardial tissue characterization, motion-corrected *T1 mapping* based on the Modified look-locker inversion recovery technique (MOLLI) using a 3-3-5 pattern is performed before and 15 min after contrast media application in 4Ch view and 3 short axes with basal, medial, and apical slices (imaging parameters: TR: 281.64 ms (4Ch) and 332.67 ms (SAX), TE: 1.12 ms, slice thickness: 6.0 mm, and Generalized Autocalibrating Partial Parallel Acquisition (GRAPPA) acceleration factor: 2).

Pseudonymized CMR data are transferred to the core Lab *AG Kardiale MRT* ([name] [name]) at the Department of Cardiology, Charité Campus Buch (Berlin), for further analysis. Experienced readers (Society for Cardiovascular Magnetic Resonance level III) analyzing the MR data are blinded to the clinical data. The clinical results are provided to the study patient, and in case of pathological findings that require further diagnostics or treatment, the clinical results are provided to the patients’ treating physician.

### TTE Protocol

Patients undergo TTE on the first day after enrollment. A second TTE for evaluating dynamic changes in cardiac function is attempted on the third to fifth day thereafter. Trained physicians and trained technicians conduct the examination using the ultrasonic device *Vivid T8* (GE Healthcare). The focus of the examination is the left and right ventricular systolic as well as diastolic function and morphology. According to the guidelines of the American Society of Echocardiography, images are acquired using standard views [25]. The TTE protocol includes two-dimensional imaging, M-mode measurements, color Doppler imaging and spectral Doppler imaging (continuous-wave [CW], pulsed-wave [PW], and Doppler tissue imaging [DTI]), as well as strain imaging using a 2D-speckle-tracking technique. Systolic LV function will be defined according to the *recommendations for cardiac chamber quantification by echocardiography in adults* as normal range (left ventricular ejection fraction [LV EF] 52%-72% [male]/54%-74% [female]), mildly abnormal (42%-51% [male]/41%-53% [female]), moderately abnormal (30%-40%), and severely abnormal (<30%) [26]. Values of signs suggesting pathologic RV systolic function are defined as TAPSE (tricuspid annular plane systolic excursion) <17 mm and s’ velocity <9.5 cm/s [27]. In addition, diastolic function will be evaluated according to the criteria of the Heart Failure Association of the European Society of Cardiology [28]. An independent rater blinded to clinical information will evaluate the echocardiographic data.

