### Sample Size Calculation and Statistical Analysis

Regarding the primary hypothesis and based on the published literature, we expect a rate of acute myocardial edema on T2 mapping in CMR in approximately 15% of patients with acute myocardial injury [17,36]. In the comparison groups with no or chronic myocardial injury, we expect a significantly lower rate (approximately 2%) presenting with acute myocardial edema [37].

To show a significant difference between the groups (two-sided α=.05), a sample size of 48 patients per group is required to reach a power of 80% and 89 patients per group for a power of 90%. Taking into consideration that in previous studies, due to impaired compliance or technical problems, the complete protocol of CMR could be realized only in approximately 85% of the study patients, we aim to include approximately 100-105 patients in each group.

Group comparisons (when comparing between the 3 groups) of the primary and secondary outcome measures (frequencies of specific alterations in CMR, TTE, and ECG) will be conducted using the chi-square test for categorical variables and, in case of continuous variables, using one-way analysis of variance or Kruskal-Wallis test, as appropriate. When comparing 2 groups (group 3 vs group 1 or group 3 vs group 2), Student *t* test will be used to compare continuous data. Logistic regression analyses will be used to calculate odds ratios and 95% CI to examine the association between elevated hs-cTn levels and the presence of specific structural and functional cardiac alterations in CMR and TTE. Multiple regression analyses using backward selection will be used to identify factors associated with certain myocardial alterations or ECG findings.

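### The male LVEF bands for echocardiography do not meet: a man with LVEF 41% falls between mildly and moderately abnormal and has no grade

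*Protocol article*

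**What the plan says.** The TTE Protocol section of the protocol article introduces the grading with "Systolic LV function will be defined according to the" and names published chamber-quantification recommendations as the source. It then prints the bands. Normal is "52%-72% [male]/54%-74% [female"]. The abnormal classes are "mildly abnormal (42%-51% [male]/41%-53% [female]), moderately abnormal (30%-40%), and severely abnormal (<30"%). The normal and mild bands are given separately for men and women. The moderate and severe bands are printed once, without a sex label.

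The study endpoints (Study Outcomes, Textbox 3) list, among the primary outcome measures, how often systolic and diastolic left ventricular function is impaired on echocardiography. Under Sample Size Calculation and Statistical Analysis, the three troponin groups are compared on such frequencies with the "chi-square test for categorical variables".

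The article gives no LVEF threshold for impaired, no rounding rule, and no other text that would place a man at 41%.

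**The concern.** A grading scheme that defines an outcome should give every possible value in the affected range exactly one class. For men this one does not, because there is a whole-percent hole between the mild and moderate classes.

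The hole lies in the reduced-function range, which bears on the study's expectations: the Discussion anticipates more change in left ventricular systolic and diastolic function among patients with dynamic troponin elevation. The TTE bands are also the only LVEF criteria the article prints for the echocardiographic primary outcome. If an analyst codes the four classes as printed and then adds the three abnormal ones to obtain the impaired count, a man at 41% drops out of that count. Depending on how the missing class is handled, he is either excluded from the comparison or counted as not impaired, although his LVEF is well below normal.

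**Working it through.** **Inputs.** All limits come from the TTE Protocol section. They are printed in whole percent, so LVEF is assumed to be recorded in whole percent. The article derives no figure on this point, so there is none to reproduce; the check is whether adjacent bands meet.

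**Step 1: do adjacent bands meet?** With whole-percent values, two bands are contiguous when the lower limit of the upper band minus the upper limit of the lower band equals 1. The severe class, below 30%, has 29% as its highest whole value.

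| Boundary | Men | Women |
|---|---|---|
| severe to moderate | 30 − 29 = 1 | 30 − 29 = 1 |
| moderate to mild | 42 − 40 = **2** | 41 − 40 = 1 |
| mild to normal | 52 − 51 = 1 | 54 − 53 = 1 |

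Only the male moderate-to-mild boundary fails. Checking each whole-percent value against the bands gives the same result. For men, 41% matches no class and is the only gap below the normal range. For women, every value from 0% to 74% matches exactly one class.

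**Step 2: does the gap reach the primary outcome?** Two derivations of impaired systolic function are possible from the printed text.

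- *Sum of the three abnormal classes.* Men: below 30, 30 to 40, and 42 to 51. Women: below 30, 30 to 40, and 41 to 53, which is every value below 54.
- *Below the lower limit of normal.* Men: below 52. Women: below 54.

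For women the two sets are identical. For men they differ by exactly one value, 41%. A man at 41% is 52 − 41 = 11 points below the male lower limit of normal. The second derivation therefore counts him as impaired, and the first does not.

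**Step 3: which edit closes the gap?**

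- Lowering the male mild limit from 42% to 41% gives 41 − 40 = 1 and leaves every other printed band as it is.
- Raising the moderate upper limit from 40% to 41% for both sexes closes the male gap, but puts a woman at 41% in two classes, since the female mild band starts there.
- Raising it for men only also closes the gap, but requires a sex-specific moderate limit that the article does not print.

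The first is the only single-number change that fits all the other bands. That is an inference from the printed text; the cited recommendations are not available here, so it does not establish which limit was misprinted.

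**The case against.** The strongest reply is that nothing of consequence depends on the gap. The listed outcome is a frequency of impaired function, not a distribution over severity grades. The classes on either side of 41% are both abnormal, so on the natural reading such a man is impaired wherever the boundary falls, and the group frequencies and chi-square comparison do not change. The grading also refers to a published source and is applied by an independent blinded rater, and the gap looks like a one-digit misprint.

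Most of this stands and limits the size of the point. It does not remove it. The article never says that impaired means below normal, and the bands are the definition it prints, so the literal coding that loses a man at 41% is open to an analyst.

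Three stronger readings are tempting, and the document does not support them:

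- *That different grades for men and women at the same LVEF are an error.* The normal and mild bands are sex-specific by design. At 52% and 53%, for example, a man is normal and a woman mildly abnormal. At 41% the defect is only that men have no grade.
- *That values above 72% (men) or 74% (women) are wrongly left unclassified.* All three abnormal classes lie below the normal range, and nothing suggests that a high LVEF would count as impaired. This is at most detail that a condensed article can leave to the full protocol or analysis plan.
- *That a particular number of the 300 patients is affected.* The article gives no LVEF distribution, so no count can be supported.

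**Conclusion.** The point holds as a small, definite error in a stated definition. As printed, the male mild and moderate bands leave out 41%, while the female bands are contiguous. The effect on the primary outcome depends on a choice the article does not make. If impaired is built from the three abnormal classes, a man at 41% is omitted. If it means below the sex-specific lower limit of normal, he is counted and only his severity grade is lost. The second reading is the more natural one, so the likely effect on the group comparison is nil or very small.

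A reader might infer that the echocardiographic primary outcome is unreliable, or that the male mild limit has been shown to be wrong. Neither follows. The gap is one whole-percent value in one sex, and the document shows that two limits do not meet without showing which one is at fault. The conclusion assumes LVEF recorded in whole percent and a moderate class that applies to both sexes as printed.

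**What to change.** 1. Check the male mild and moderate limits in the TTE Protocol section against the cited recommendations and correct them so that the bands are contiguous. Lowering the male mild limit to 41% is the single-number edit that fits the other printed bands; adopt it only once the source confirms it.
2. Add one sentence deriving impaired systolic function on echocardiography directly from the article's own lower limits of normal: LVEF below 52% in men and below 54% in women. The primary outcome then no longer depends on where the mild and moderate classes meet.

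The cost is a check against the source, one corrected number and one sentence. No additional data, patients or measurements are needed. Both changes should be settled before the echocardiographic outcome is coded.
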